**Fig 1 pone.0295994.g001:**
[figure not shown]
The SPIRIT schedule of enrolment, interventions and assessments for the RECONCILE study.

## 3. Objectives

The RECONCILE study will characterise the molecular changes and other factors associated with first identifiable radiological progression event in early Gleason 3 + 4 prostate tumours. Deep phenotyping of the MRI lesion in question will inform novel strategies for improved baseline disease risk stratification.

### 3.1 Primary objective

The primary objective is to estimate the association of molecular changes with radiological progression events of small, localised Gleason 3 + 4 tumours visible on mpMRI.

### 3.2 Secondary objectives

Secondary objectives will assess the impact and associations of radiological tumour progression on a broad set of criteria. Specifically, the secondary objectives will:

*Examine the effect of progression on*:

Mechanistic events occurring at genetic, epigenetic, transcriptomic and proteomic levelImaging features of the MRI lesion in question as well as the rest of the glandDigital pathology (cancer and benign tissue)Tumour microenvironementImmune contexture of prostate cancer and prostate tissueTransition to active treatment and any impact upon eligibility for available treatment optionsPatient reported quality of life outcomesRecurrence after treatment and progression to metastasis

*Derive*:

Progression endotypes (cohorts) based on genetic, epigenetic, transcriptomic, and proteomic immune determinants of MRI progressionA predictive model of progression based on molecular analysis, imaging, histology and clinical dataTime to radiological progressionData to inform existing health economic modelling

*Refine*:

A molecular index (MoI) of progression derived from analyses of biopsies at baseline and at a 12-month intervalA model of progression as stochastic, deterministic or a transition between the two at molecular analysis

*Assess*:

Inter-observer variability of the PRECISE score [11] and MRI lesion segmentationFeasibility and acceptability of a novel system of care driven by a demonstrable phenotype at baseline rather than clinical risk estimation

### 3.3 Exploratory objectives

Exploratory objectives will assess any parameters linked to progression, including to invasive prostate cancer treatment and any clinically relevant events such as failure of primary treatment or metastasis. Clinical events will be reviewed by staff who are authorised to access patient medical records during longitudinal follow up.

## 4. Study design

### 4.1 Study entry

Participants may enter RECONCILE following participation in the ReIMAGINE Prostate Cancer Risk Study (NCT04060589) or at the time of tertiary referral for disease re-stratification (Fig 2). The ReIMAGINE Risk Study is running concurrently at site and provides a platform for deeply phenotyping prostate mpMRI lesions (>/ = Likert / PI-RADS 3) through molecular and radiomic analysis [18].

**Fig 2 pone.0295994.g002:**
[figure not shown]
A & B: RECONCILE participant pathway.

Participants recruited following participation in ReIMAGINE Risk will consent to the sharing of their biological samples and MR imaging with RECONCILE. Therefore, no additional baseline interventions are required for those recruited to RECONCILE from ReIMAGINE. Participants will, however, consent to donation of tissue and MRI data at one year.

An alternative route of entry is at the time of standard of care confirmatory targeted biopsy. This will normally follow a specialist referral to our centre for disease re-stratification and/or management. Such patients must have been diagnosed with Gleason 3 + 4 prostate cancer within 12 months of entry to RECONCILE and meet all other eligibility criteria. Research samples (blood, urine and prostate tissue) will be collected at the time of standard of care confirmatory targeted prostate biopsy. A repeat mpMRI prostate is also required as per local NHS protocol, a copy of which will be used for research. Interval research samples will be collected at one year.

### 4.2 Exposure variable

The main exposure variable is the deep phenotyping of the MRI-visible lesion at baseline and one year. This will be achieved using donation of tissue from additional targeted sampling (using visual-estimation) of the MR-visible lesion of interest harbouring Gleason 3 + 4 disease. A control sample collected from an area of unremarkable tissue on MRI (Likert / PI-RADS v2.1 score 1 or 2) will further inform the characterisation of the MR lesion.

### 4.3 Generation of the population for association between molecular changes and radiological progression

RECONCILE will identify molecular changes associated with radiological progression events in localised Gleason 3 + 4 tumours. Investigators assessing molecular and radiological changes at baseline and one year will be kept blinded to the results of each outcome.

A contingency table will be generated to assess the interrelation between radiological progression and molecular changes. The table will include the following variables: radiological progression (R+), radiological non-progression (R-), Molecular changes (M+), no molecular changes (M-). The contingent for each subgroup to maintain association will be calculated for a set precision to capture significant molecular changes and assess the interaction between molecular change and radiological progression.

### 4.4 Assessment of molecular change

We have designed a molecular analysis strategy that accounts for three potential pitfalls which need to be overcome: tumour content, sampling bias and spatial heterogeneity of the tumour.

#### 4.4.1 Molecular index

We will use next-generation sequencing and expression analyses to derive a quantitative molecular index for every baseline (MolBL) and follow-up (MolFU) biopsy. For each individual patient, the difference in the baseline molecular index between the two baseline biopsy samples (ΔMolBL) will be calculated. This is a measure of intrinsic patient tumour heterogeneity and will identify molecular features which are consistent between lesions, overcoming sampling bias. The relationship of the targeted biopsy sample to the longitudinal axis of the cancer lesion will also be taken into account using multi-slice processing and separate processing of the sample extremities.

We will use the same metrics to generate a MolFU for each patient using per protocol follow-up biopsy samples. We will then compare MolBL and MolFU for every individual patient and extract a ΔMolBL:MolFU score. Patients will be classified as having a molecular progression event if the ΔMolBL:MolFU score is greater than 95% CI of the combined ΔMolBL scores. Researchers generating the molecular index score will be blinded to radiological progression annotations.

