### 8. Statistical analysis

The primary statistical analysis will be to estimate the association of match‐paired binary responses (molecular and radiological progressors) since the results of the two tests are not independent. For McNemar’s test of paired proportions using the Miettinen normal approximation with a two‐sided significance level of 0.05, a sample size of 60 achieves a power of at least 0.8 when the discordant proportions are 0.05 (5%) and 0.25 (25%) of the total number. The ratio of progressors will inform the precision of the IC for the molecular analysis. Study results will be shared in peer reviewed journal articles.

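### The molecular change score is quantitative, but for the association objective it meets radiological progression only after a yes/no cut; a named analysis of the continuous score should stand beside the 2x2 table

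*Protocol article*

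**What the plan says.** Section 3.1 of the protocol article sets the primary objective: to estimate the association of molecular changes with radiological progression.

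Section 4.4.1 plans "to derive a quantitative molecular index for every baseline" and follow-up biopsy, and a baseline-to-follow-up change score per man. It then makes the score binary: "Patients will be classified as having a molecular progression event if the" change score lies above the 95% CI of the combined differences between the two baseline cores.

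Section 4.3 states how the two measures meet: "A contingency table will be generated to assess the interrelation between radiological progression and molecular changes", with R+/R- crossed against M+/M-. Section 7.1 makes the proportion of concordant pairs of progressors the primary outcome. Section 8 analyses the paired binary responses by McNemar's "test of paired proportions using the Miettinen normal approximation".

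The cut-off is described in two ways. Section 4.4.1 takes it from baseline heterogeneity. Sections 4.6.1 and 4.6.2 instead derive, once the radiological classes are known, the minimum precision needed to maintain the association, and apply it to decide who is a molecular progressor.

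The index is listed as a secondary outcome in section 7.2, and section 3.2 plans a predictive model. Neither states a test of the continuous change score against radiological progression for the primary objective.

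**The concern.** For an association objective, a cut before the comparison discards how far each man's score moved. A man just above the limit counts the same as one far above it, and a man just below counts as no change. With 60 men that information is not easily spared.

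The result also hangs on where the cut falls. Because sections 4.4.1 and 4.6 do not place it by the same rule, the M+ label can move, and the estimated association moves with it. An analysis of the score itself needs no cut-off.

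**Working it through.** **1. The plan's own figure.** Section 8 says that "a sample size of 60 achieves a power of at least 0.8". The test is two-sided at 0.05, and the two discordant cells are put at 5% and 25%. The discordant total is ψ = 0.05 + 0.25 = 0.30, the difference is d = 0.25 − 0.05 = 0.20, and n = 60. Miettinen's second-order approximation gives

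Φ[(d√(nψ) − zψ) / √(ψ² − d²(3+ψ)/4)] = Φ[(0.2 × 4.243 − 1.96 × 0.30) / √(0.09 − 0.033)] = Φ(0.2605/0.2387) = Φ(1.09) = 0.862.

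The stated power of at least 0.8 is reproduced.

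**2. Why the loss cannot be taken off that figure.** McNemar's test compares the marginal rates of M+ and R+. With discordant cells 0.25 and 0.05, the odds ratio is p11·p00/(0.25 × 0.05):

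- 2% concordant positive: 0.02 × 0.68 / 0.0125 = 1.09
- 15% concordant positive: 0.15 × 0.55 / 0.0125 = 6.6

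The approximation in step 1 gives 0.862 in both cases, so it says nothing about power for association.

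**3. Information lost by the cut.** Assume a normal score and let q be the share above cut c. The asymptotic relative efficiency of the binary version is φ(c)²/[q(1−q)].

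| Share M+ | Efficiency | Information lost |
|---|---|---|
| 50% | 0.637 | 36% |
| 30% | 0.576 | 42% |
| 20% | 0.490 | 51% |
| 10% | 0.342 | 66% |

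The smallest loss, at the median, is 0.1592/0.25 = 0.637, so 36%.

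**4. Power under a uniform shift.** Assumed: n = 60, R- men N(0,1), R+ men N(1,1), M+ if the score exceeds 1.645 (the upper 5% point of no change), 9 to 24 R+ men, two-sided 0.05. Simulated power:

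| Analysis | Power |
|---|---|
| Fisher on the 2x2 table | about 39-56% |
| Uncorrected chi-square on the 2x2 table | about 57-65% |
| Logistic regression on the score | about 80-96% |

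Fisher is conservative in tables this sparse, so part of its gap comes from the test and not the cut. The chi-square row is the fairer comparison.

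**5. How far the size moves.** The shift was next set so that a t-test on the score has about 80% power, with 6 to 24 R+ men.

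- 20-50% M+: the cut leaves 0.53-0.68 (chi-square) or 0.42-0.61 (Fisher).
- 10% M+: it leaves 0.36-0.67 or 0.28-0.52.

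The relative loss of power runs from 14% to 66% over all settings.

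**6. A different pattern of effect.** Now only 30-40% of R+ men change, by 3 to 4 SD, and the rest do not. The cut is again 1.645, with 9 to 24 R+ men.

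| Analysis | Power |
|---|---|
| Wilcoxon on the score | about 33-72% |
| Fisher on the 2x2 table | about 56-91% |
| Logistic regression on the score | about 64-89% |
| Uncorrected chi-square on the 2x2 table | about 71-94% |

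Here the cut costs nothing. The rank test does worse than the table, while logistic regression stays roughly level with Fisher and somewhat below chi-square.

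**The case against.** The cut has a purpose. Sections 4.4 and 4.4.1 use the difference between two baseline cores as a yardstick for sampling and spatial heterogeneity, so that a change must exceed it to count. The primary outcome is concordance between two kinds of progressor, which needs two binary classes. An odds ratio per SD answers a neighbouring question, not the same one. This stands, and it is why the binary outcome should stay.

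The size of the loss is model-dependent. The article speaks of a molecular progression event and plans progression endotypes, so a sharp change in some men is as compatible with it as a uniform shift. Step 6 shows that the loss can then vanish. This also stands, and it rules out simply making a rank test primary.

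The continuous index is kept as a secondary outcome, and an analysis plan not shown may add supportive analyses. This stands only in part: the article itself fixes the primary comparison as binary, and the places where it keeps the index do not tie the continuous score to the association objective.

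Four stronger readings are tempting and are not supported:

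- **A third of the power is lost.** About 36% is the information lost at a median cut; the loss of power has no fixed value.
- **There are few progressors.** No progression rate is given, and the discordant proportions do not fix one.
- **Only R+ men carry information.** R- men supply the comparison in either analysis.
- **The stated 80% is thereby reduced.** It belongs to a test of marginal rates (step 2).

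**Conclusion.** The point holds in a limited form. For its association objective the article compares a quantitative score with radiology only after a yes/no cut, at a cut-off that it describes in two ways. Under a normal score with a uniform 1 SD shift the cost is substantial: chi-square power on the table is some 23 points below logistic regression at the low ends of the two ranges (80 − 57) and 31 at the high ends (96 − 65). Under a sharp change in a subset it is nil. The progression rate, the distribution of the index and the pattern of effect are all assumed here. What does not depend on them is that the planned association result rests on the cut-off, and that an analysis free of it can be run on the same data.

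**What to change.** Keep the concordance outcome and the 2x2 table. Beside them, pre-specify logistic regression of radiological progression on the continuous baseline-to-follow-up change score as the named key analysis of the association objective. Report the odds ratio per SD with its 95% CI, and the AUC. Logistic regression is preferable to a rank test here because it holds up better when only some men change.

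Sections 4.4.1, 4.6.1 and 4.6.2 should also give one rule for the cut-off behind the table; the continuous analysis does not depend on it.

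The cost is one more analysis and its wording, with no new participants, samples or assays. The effect measure is less familiar to clinical readers than a 2x2 table.

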### 6.5 Prostate tissue collection

Consenting patients will donate three additional cores of prostate tissue at the time of their baseline standard of care prostate biopsy. At exit, participants will donate a further 3 biopsy tissue cores, or five additional cores if there is a new lesion on mpMRI. Cores 4 and 5 will be collected from the highest scoring, greatest volume new lesion.

We do not anticipate that collection of additional tissue cores for research will increase the likelihood of side effects or adverse events relative to standard of care biopsy alone. The risks and adverse outcomes of prostate biopsy quoted within the RECONCILE patient information sheet are outlined in Table 3. Research cores will be targeted using visual-estimation to areas of interest identified on pre-biopsy mpMRI. Research cores will only be attempted after all required standard of care diagnostic biopsies have been collected.

**Table 3 pone.0295994.t003:** Side effect profile of a targeted transperineal prostate biopsy as stated in the RECONCILE study patient information sheet.

Side effect	Proportion of men	Duration
Pain/discomfort in back passage	Almost all	Temporary for 1–2 days
Burning when passing urine	Almost all men	Self-resolving, 1–3 days
Bloody Urine	Almost all	Self-resolving, 1–7 days
Bloody Sperm	Almost all	Lasting up to 3 months
Poor erections	1–2 in 100	Temporary for 1–6 weeks
Infection of skin/urine	1–2 in 100	7 days with treatment with antibiotics
Infection of skin/urine needing admission and intravenous antibiotics	Less than 1 in 500	7–14 days with treatment with antibiotics. Rarely up to 28 days of antibiotics after leaving hospital.
Difficulty passing urine requiring catheter placement for up to a week. A catheter is a soft plastic tube placed into the bladder to drain urine.	1 in 100	3–7 days
Bruising of skin	Almost all	Self-resolving, 7–14 days
Bruising spread to scrotum	1 in 100	Self-resolving, 7–28 days

All cores will be collected in line with the study Tissue Collection SOP. The first and second research cores will be collected from the centre of the lesion with the highest Likert / PIRADS score and greatest volume (lesion 1). Lesion volume will be determined by MRI reporting.

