The third research core will be collected from an area of non-suspicious (Likert / PIRADS score 1 or 2) tissue. Should new MRI lesions be visible at the time of exit from the study (minimum Likert / PIRADS score 4), two additional tissue cores (Cores 4 and 5) may be collected from the centre of the new highest scoring, greatest volume lesion. Table 4 summarises the location from which to collect each prostate biopsy core.

**Table 4 pone.0295994.t004:** Prostate tissue sampling locations for the RECONCILE study.

Research Core	Lesion to target	Area within lesion to target	Casette colour
Core 1	Lesion with highest PIRADS / Likert score and greatest volume (lesion 1)	Centre of the lesion	Pink
Core 2	Same lesion as above (lesion 1)	Centre of lesion 1	Green
Core 3	Contralateral nonsuspicious area	Any non-suspicious radiological area, either contralateral lobe or TZ if bilateral lesions or diffuse changes in bilateral lobes	Yellow
Core 4 (optional)	New radiological lesion with the highest PIRADS/LIKERT score at interval assessment (lesion 2)	Centre of lesion 2	Any colour, labelled as Core 4
Core 5 (optional)	New radiological lesion with the highest PIRADS/LIKERT score at interval assessment (lesion 2)	Centre of lesion 2	Any colour, labelled as Core 5

The location of each prostate core will be recorded within a study CRF (Fig 4) and each core placed within a colour coded pathology cassette before being placed within PAXgene® tissue fixative. Samples will be fixed in PAXgene® Tissue Fix reagent for at least 2–24 hours. Cores are then treated with PAXgene® Tissue Stabalizer concentrate and ethanol for at least 2 hours. All pseudonymised samples will be logged to the FreezerPro database and stored at -80°C following stabiliser treatment. All biological samples are processed and stored in line with the RECONCILE Laboratory Manual.

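### The limit for molecular progression is built from same-session core differences, so it leaves out variation between visits and the false-positive rate of the label is not controlled

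*Protocol article*

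**What the plan says.** Section 4.4.1 derives a molecular index for every biopsy. Its noise reference, ΔMolBL, is "the difference in the baseline molecular index between the two baseline biopsy samples" within a patient, and the section describes it thus: "This is a measure of intrinsic patient tumour heterogeneity and will identify molecular features which are consistent between lesions, overcoming sampling bias". A patient is a molecular progressor (M+) if the "ΔMolBL:MolFU score is greater than 95% CI of the combined ΔMolBL scores".

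Section 6.5 shows where the two baseline samples come from. "Consenting patients will donate three additional cores of prostate tissue at the time of their baseline standard of care prostate biopsy". Of these, "The first and second research cores will be collected from the centre of the lesion with the highest Likert / PIRADS score and greatest volume", and Table 4 repeats that core 2 is aimed at the centre of the same lesion as core 1. "The third research core will be collected from an area of non-suspicious" tissue, at baseline and again at exit. On method: "Research cores will be targeted using visual-estimation to areas of interest identified on pre-biopsy mpMRI".

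Under section 5.2 the exit MRI and biopsy normally follow 12 months after baseline tissue collection, or sooner if progression is suspected. Participants entering from the ReIMAGINE Risk study use shared baseline samples (sections 4.1 and 5.2), and the core layout of those samples is not described.

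The M+/M- label forms one side of the contingency table (section 4.3), the primary outcome (section 7.1) and the McNemar test (section 8).

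**The concern.** A limit for change should contain every source of noise that the change score contains when nothing has truly changed. Two cores from one session share the same pre-biopsy MRI, the same biopsy session and the same handling conditions. Whatever they share cancels in core 1 minus core 2. It does not cancel between baseline and exit, where there is a new MRI, a new visual estimate of the lesion centre, and a fixation time that section 6.5 gives only as a range (2–24 hours). Some patients' baseline tissue also comes through another study.

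The scale of the two quantities is a further issue. ΔMolBL is a core-against-core difference, while MolFU is described per patient. If the patient value averages two cores, the limit and the score have different within-visit variances even before any visit effect is added.

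At stake is how many stable patients are labelled M+. In the section 8 design the smaller discordant cell is 5% of 60, or 3 pairs, so a handful of wrong labels matters.

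**Working it through.** **The plan's own figure.** Section 8 states power of at least 0.8 for N = 60 with discordant proportions 0.05 and 0.25. The total discordant proportion is ψ = 0.30 and the difference is d = 0.20. Miettinen's approximation gives

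power = Φ[(d√(Nψ) − 1.96ψ) / √(ψ² − d²(3+ψ)/4)] = Φ[(0.8485 − 0.588)/√0.057] = Φ(1.09) = 0.862.

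The stated power reproduces and is not disputed. It takes the M+ label as given, and the question here is how the label behaves.

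**Inputs for the label.**
- From the documents: the reference is core 1 minus core 2 at baseline; the score is exit against baseline; the rule is one-directional (greater than the limit).
- Assumed: normal errors, no true molecular change, and the 95% CI read as a one-sided 95% reference limit (z = 1.645).
- Assumed, because the documents give no value: t, the between-visit variance per visit divided by the single-core variance s², taken from 0 to 2. Set s² = 1.

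**Formulas.**
- Reference SD = √(1 + 1) = √2, so the limit is 1.645√2 = 2.326.
- Score SD with one core per visit = √(2 + 2t).
- Score SD with two-core means = √(½ + ½ + 2t) = √(1 + 2t).
- False M+ rate = 1 − Φ(2.326 / score SD).

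| t | Single cores: SD | False M+ | Two-core means: SD | False M+ |
|---|---|---|---|---|
| 0 | 1.414 | 5% | 1.000 | 1% |
| 0.5 | 1.732 | 9% | 1.414 | 5% |
| 1 | 2.000 | 12% | 1.732 | 9% |
| 2 | 2.449 | 17% | 2.236 | 15% |

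Single cores are at 5% only when t = 0. Two-core means are at 5% only when t = 0.5; the rule is too strict below that and too lenient above it.

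**Sensitivity to sidedness.** With a two-sided range (|difference| > 1.96√2) and t = 0, 0.5, 1, 2, the rates are 5.0, 11.0, 16.6 and 25.8% for single cores, and 0.6, 5.0, 11.0 and 21.5% for two-core means. The pattern is the same.

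**Effect of aligning the scale alone.** For two-core means the matched limit is 1.645 × 1 = 1.645. The false M+ rate is then 1 − Φ(1.645/√(1+2t)), which is 5, 12, 17 and 23% at the same four values of t. Matching the scale removes an accidental offset, so it must go together with some handling of between-visit variation. A limit of 1.645√(1+2t) would hold 5% throughout, but same-session pairs cannot estimate t.

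**What this means in counts.** If 40 of 60 participants were radiological non-progressors (assumed), rates of 5–17% would put 40 × 0.05 = 2 to 40 × 0.17 ≈ 7 stable patients in the discordant cell with M+ and no radiological progression. At 1–15% it would be about 0 to 6. The two discordant cells in section 8 are 3 and 15 patients.

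**The case against.** **The size is not document-based.** This stands. The ratio t is assumed, and the range includes 5%, so a reader who infers that the rule over-labels goes further than the documents allow. They show that the rate is uncontrolled, not that it is high.

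**Much of the noise is already in ΔMolBL.** This also stands. Every biopsy has its own index and each core is aimed by visual estimation, so within-run assay noise and core-to-core targeting error are in the reference. Only the part shared by all cores of a visit is missing. The run-related part would vanish if paired samples were assayed together, which no section rules out.

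**Other provisions help.** Section 4.4.2 has each core run along the lesion's long axis, with multi-slice processing and separate analysis of the extremity. That deals with position along the core, not with differences between visits. Sections 4.6.1 and 4.6.2 add a precision step derived from the contingency table, which is not an estimate of between-visit noise.

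**It may be left to an analysis plan.** Details of aggregation and batching may be. The yardstick itself is not, because section 4.4.1 fixes it and claims that it overcomes sampling bias.

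**Differential error.** A reader might infer that re-targeting error is larger in lesions that grew, and so imitates an association with radiological progression. That is possible, since volume is a key component of PRECISE (section 1.1). Nothing in the document shows that it happens or in which direction.

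**Core 3 as an estimate of visit noise.** It is tempting to estimate the between-visit variance directly from core 3. Table 4 lets that core come from any non-suspicious area and does not require the same site twice, so it cannot give a clean estimate for the lesion.

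**Conclusion.** The point holds in a limited form. As written, section 4.4.1 compares a between-visit score with a purely within-session limit, and no other section supplies the missing variance. Under a one-sided 95% reference limit and t from 0 to 2, the false M+ rate is 5–17% for single cores and 1–15% for two-core means, against a nominal 5%. These figures rest on normal errors and an assumed variance ratio, and the direction of the error is open. The same-spot, same-session layout is documented only for cores collected within RECONCILE. Because the label feeds the primary outcome directly, the rule should be amended before the molecular data are classified. The evidence does not support saying that the label is known to be inflated, or that the error is known to track lesion growth.

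**What to change.** In section 4.4.1:

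1. Compute the reference limit on the same scale as the patient-level change score, with the same number of cores averaged on both sides. Do this together with steps 2 and 3, since aligning the scale alone can raise the false M+ rate when between-visit variation is present.
2. Assay each patient's baseline and exit cores in the same batch, so that between-run effects cancel.
3. Apply the same M+ rule to the baseline-to-exit change in core 3 and report that rate as a negative control. Add a sensitivity analysis that widens the limit by a between-visit component informed by core 3.

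Cost: more analysis and some sample scheduling, but no extra tissue, because the cores are already collected and stored at -80°C. Section 10.1 already names the non-suspicious core as the control. There are two downsides. Sequencing of baseline cores must wait for exit samples. Core 3 is benign tissue that need not be resampled at the same site, so its change mixes location differences with visit noise and is only an approximate guide.

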**Methods:**

RECONCILE is an ethics approved (20/LO/0366) single centre, prospective, longitudinal, observational cohort study of recently diagnosed (within 12 months), organ-confined Gleason 3 + 4 cancers (MCCL ≤10mm) currently under active surveillance. 60 treatment-naïve participants with a concordant MRI lesion (Likert score 4 or 5) and PSA ≤ 15 ng/ml will be recruited.

Blood, urine and targeted prostate tissue cores will be subject to next generation sequencing at baseline and one year in all participants. Semen will be collected from a specified sub-population. Baseline and interval MR images will be extracted from standard of care prostate MRI ahead of radiomic analysis. Data extracted from radiological and biological samples will be used to derive the association of molecular change and radiological progression, the primary outcome of the study.

To compensate for spatial intratumoral heterogeneity and inherent sampling bias, a molecular index will be derived for each participant using the molecular profile of tumour tissue at both baseline (MolBL) and one year (MolFU). We will extract a ΔMolBL:MolFU score for each participant. Molecular progression will be defined as a MolBL:MolFU score >95% CI of the combined ΔMolBL scores. Radiological progression is defined as a PRECISE score of 4 or 5. The study is powered to detect an association with a statistical power of 80%.

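### The same baseline core-to-core differences identify the index features and set the limit for molecular progression; if the index is built from those features, the limit is biased narrow

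*Protocol article*

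**What the plan says.** Section 4.4.1 of the protocol article defines the noise measure: "For each individual patient, the difference in the baseline molecular index between the two baseline biopsy samples (ΔMolBL) will be calculated". It then gives that measure two uses.

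- Feature identification: "This is a measure of intrinsic patient tumour heterogeneity and will identify molecular features which are consistent between lesions, overcoming sampling bias". Both paired cores come from one lesion (section 6.5: "The first and second research cores will be collected from the centre of the lesion"), so agreement here can only mean agreement between cores.
- Limit for change: "Patients will be classified as having a molecular progression event if the ΔMolBL:MolFU score is greater than 95% CI of the combined ΔMolBL scores". The Methods part of the abstract repeats the rule: "Molecular progression will be defined as a MolBL:MolFU score >95% CI of the combined ΔMolBL scores".

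The follow-up index is tied to the baseline one: "We will use the same metrics to generate a MolFU for each patient using per protocol follow-up biopsy samples". The article mentions no held-out men, no cross-validation and no feature list fixed beforehand. The blinding in this section concerns radiology only: "Researchers generating the molecular index score will be blinded to radiological progression annotations".

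**The concern.** Features kept because two baseline cores agreed have small baseline differences partly by chance. If exit cores play no part in that choice, their differences on the same features return to their true size. A limit calibrated on the selected baseline differences is then too narrow for the follow-up differences it judges, and some unchanged men cross it for that reason alone. The error runs one way: compared with an honest limit for the same index, it can only add M+ calls.

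M+ status is half of the primary outcome in section 7.1 (concordance of molecular and radiological progressors) and feeds the McNemar test in section 8. False M+ calls in men without radiological progression fall in one discordant cell.

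**Working it through.** **The plan's own figure.** Section 8 gives power of at least 0.8 with N = 60, discordant proportions 0.05 and 0.25, and two-sided alpha 0.05. With ψ = 0.30 and δ = 0.20, Miettinen's power is Φ[(√(Nψ)·δ − 1.96ψ) / √(ψ² − δ²(3 + ψ)/4)] = Φ[(4.243 × 0.20 − 0.588) / √(0.090 − 0.033)] = Φ(0.2605/0.2387) = Φ(1.091) = 0.862. The figure holds. The article gives no false M+ rate, so that has to be modelled.

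**Assumptions (none in the article except N = 60).** 1,000 independent normal features; index = mean of the kept features; no man changes; limit = 1.96 × SD of ΔMolBL, with change in either direction counted; features kept for the smallest baseline core-to-core difference. For features that truly differ in noise, the feature SDs are log-normal with log-SD 0.25 or 0.5.

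**Scale.** With core variance σ², Var(ΔMolBL) = 2σ². Follow-up against baseline has variance 2σ² for single cores, but σ²/2 + σ²/2 = σ² for means of two cores. In the second case the null follow-up SD is 1/√2 = 0.71 of the ΔMolBL SD, and without selection the false rate is 2[1 − Φ(1.96 × 1.414)] = 0.6%.

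**Results.** The ratio is SD of selected ΔMolBL / SD of the follow-up difference. The approximate rate is 2[1 − Φ(1.96 × ratio)]. The simulated rate tends to run slightly higher because the SD is estimated.

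| Comparison | Selection (share of features kept) | Ratio | Approximate rate | Simulated rate |
|---|---|---|---|---|
| Single core | none | 0.99 | 5.2% | 5.6% |
| Single core | cohort, equal noise, 50% | 0.94 | 6.5% | 7.1% |
| Single core | cohort, equal noise, 10% | 0.88 | 8.5% | 9.3% |
| Single core | cohort, equal noise, 1% | 0.81 | 11.2% | 12.1% |
| Single core | cohort, unequal noise | 0.95-0.99 | 5.2-6.3% | 5.6-6.9% |
| Two-core mean | none | 1.43 | 0.5% | 0.6% |
| Two-core mean | cohort, equal noise, 50% / 10% / 1% | 1.33 / 1.20 / 1.10 | 0.9 / 1.9 / 3.1% | 1.3 / 2.2 / 3.6% |
| Two-core mean | cohort, unequal noise | 1.28-1.40 | 0.6-1.2% | 0.9-1.6% |
| Single core | man by man, 50% / 10% / 1% | 0.43 / 0.09 / 0.01 | 40 / 86 / 98% | 40 / 87 / 98% |
| Two-core mean | man by man, 50% / 10% / 1% | 0.54 / 0.10 / 0.01 | 29 / 84 / 98% | 30 / 84 / 98% |

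**Is the reuse the cause?** Selecting 10% of features in half the men and setting the limit in the other half gives 5.1-5.4% (single core) and 0.7-1.1% (two-core mean). With reuse the same settings give 6.3-9.3% and 1.3-2.2%.

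**Effect on the primary test.** Assume 20% radiological progressors and no other discordance. The M+R− count is then binomial with N = 60 and probability 0.8 × f, where f is the false rate. With all discordance on one side, the exact test rejects at 6 or more pairs (2 × 0.5⁶ = 0.031; for 5 pairs, 2 × 0.5⁵ = 0.063). P(count ≥ 6) is 3% at f = 5%, 5% at 5.6%, 29% at 9.3%, 35% at 10% and 53% at 12.1%. At f = 10% it is 46% with 10% radiological progressors and 24% with 30%.

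**The case against.** **The mechanism is inferred.** In section 4.4.1 the index is derived for each biopsy and ΔMolBL is a difference in that index. No sentence says that the index is then rebuilt from the consistent features, and the same metrics at follow-up could mean only the same measurements. Nor does the article say that exit samples stay out of the choice; a secondary objective in section 3.2 is to refine an index from biopsies at both times. If they did take part, the bias would shrink. This stands, so the point must be put conditionally.

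**A reader might infer that unchanged men exceed the nominal 5% in any case.** The documents do not support this. They do not say whether single cores or two-core means are compared. With two-core means the limit would have to shrink by more than 29% (1 − 0.71) to pass 5%, and cohort-level selection shrinks it by 6-19%.

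**A reader might also infer man-by-man selection, with false rates of 30-98%.** The phrase about each individual patient governs the calculation of the difference, not the choice of features. Scores built from different features in each man could hardly be combined into one limit.

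**The limit itself is unclear.** If the 95% CI is one for the mean signed difference, its half-width is 1.96/√60 = 0.253 SD, and 72-80% of unchanged men exceed it without any selection. Sections 4.6.1, 4.6.2 and 8 also let radiological progression inform the precision for molecular change, so this limit may not be the only rule. These are separate points, and the first outweighs the present one.

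**An article leaves detail to the full protocol.** That excuses a missing feature list. It does not cover a stated rule that uses the same differences for both jobs and claims to overcome sampling bias by doing so.

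**Conclusion.** The double use is in the text and its direction is clear. If the index is built from the features that ΔMolBL identifies, and exit samples play no part in the choice, the limit is biased narrow and can only add false M+ calls.

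For cohort-level selection the size is small to moderate: about 6-12% false M+ against about 5-6% without selection when single cores are compared, and nearer 6-7% when features truly differ in noise. With two-core means it is about 1-4% against under 1%, so inflated but still below 5%. That shelter comes only from a mismatch of scale between limit and follow-up difference; it is not a designed safeguard.

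All rates rest on the assumed feature count, independence, normality and a 1.96 SD limit. They leave out variation between visits or batches, which would raise them.

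**What to change.** - State that index features are chosen at cohort level, and lock them before the limit is computed.
- For the limit, compute each man's ΔMolBL with features selected without that man (leave-one-man-out or k-fold).
- Put the limit on the same core scale, single core or two-core mean, as ΔMolBL:MolFU, and say that it refers to individual differences.
- Use exit core 1-core 2 pairs only as a sensitivity check, because progression may widen them.

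The cost is changed wording and a cross-validation loop; no new samples are needed. Removing the reuse leaves somewhat fewer men labelled M+. If two-core means are compared, matching the scale works the other way: it divides the limit by √2 = 1.41 and moves the false rate from under 1% up towards the intended 5%. It should therefore not be done without also removing the reuse.
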